## Methods

### Study setting

The study will be conducted at Moffitt Cancer Center (Moffitt) and the University of North Carolina at Chapel Hill (UNC), two Cancer Centers that serve different patient populations. Moffitt is a standalone, non-profit National Cancer Institute (NCI)designated Comprehensive Cancer Center that serves a primarily urban patient population (93%) in a region of Florida where 21% of the population is Latino/Hispanic. UNC is a public academic medical center that includes a matrix NCI-designated Comprehensive Cancer Center and affiliated community oncology clinics. UNC serves a patient population that is ~ 33% rural and 20% Non-Hispanic Black/African American.

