### Randomization

Patients (*N* = 80) will be 1:1 randomized to the STRONG program versus usual care. The study statistician will develop a randomization table using the randomization function in Stata (StataCorp. 2025. Stata Statistical Software: Release 19. College Station, TX: StataCorp LC.) that will be uploaded to REDCap^®^ (Research Electronic Data Capture). Randomization will be stratified based on cancer type and treatment modality (e.g., single versus multimodal treatment) to ensure groups are balanced on these factors, which may affect malnutrition risk. Block randomization (in variable block sizes of 4 and 6) will be used to maintain balance across groups and concealment. Outcome assessors and the study statistician will be blinded to group allocation.

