#### Aim 2 analyses

Preliminary outcomes will be measured at three time points (baseline, 3-, and 6-months) for two groups (intervention and control). We will use linear mixed-effects models to estimate changes in PG-SGA scores between groups, as they account for dependence of longitudinal assessments and allow for patients with incomplete data to be included in analyses. The model will include fixed effects for time, group, and group X time. A group X time interaction will provide evidence for differential change by treatment groups. Randomization strata and any group differences not balanced through randomization procedures will be included as covariates in the model. Recruitment site (UNC, Moffitt) will be included as a random effect in the analyses. Mean differences will be compared against the threshold for a clinically significant difference in PG-SGA score (4-point change). A similar approach will be applied for other discrete or continuously measured outcomes using MCIDs when available. We will use generalized estimating equations (GEEs) to estimate whether the change in the proportion of patients with severe malnutrition (yes/no) over time differs between the intervention and control group. A similar approach will be applied for other binary outcomes. For time-to-event outcomes (i.e., survival), we will use a stratified Cox proportional hazards model (stratified by randomization strata) and adjusted for any characteristics not balanced across groups. The primary parameter of interest is the Cox Hazards Ratio (HR). We will test model assumptions (e.g., Schoenfield residuals) and adjust the statistical approach as needed (e.g., use of time-varying HR). We will model Kaplan-Meier curves by group assignment from baseline to 6-months.

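### Recruitment site has only two levels but is modelled as a random effect; a pre-specified fixed site indicator would serve better in the mixed, GEE and Cox models (minor)

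*Protocol article*

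**What the plan says.** The Aim 2 analyses section of the protocol article specifies a linear mixed model for PG-SGA. On the fixed part it says: "The model will include fixed effects for time, group, and group X time". On covariates: "Randomization strata and any group differences not balanced through randomization procedures will be included as covariates in the model". On site: "Recruitment site (UNC, Moffitt) will be included as a random effect in the analyses". The same section plans GEEs for binary outcomes. It plans a Cox model stratified by the randomization strata and adjusted for characteristics that turn out unbalanced.

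The Randomization section says: "Randomization will be stratified based on cancer type and treatment modality". Site is not listed there, so the strata covariates do not carry it. The Study setting section calls the sites "two Cancer Centers that serve different patient populations".

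**The concern.** A random effect treats its levels as draws from a population and estimates their variance. With two named centers there is one contrast from which to estimate it. REML sets the variance to zero whenever the between-site F statistic falls below 1, and the model then contains no site adjustment. When the estimate is not zero, it is very imprecise.

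This matters in three ways:

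- Whether and how strongly site is adjusted for is decided by the data, although the plan intends to adjust.
- The pilot is meant to inform a definitive trial, and a site variance of this quality cannot do so.
- The stated device does not reach all the planned models. A standard GEE has no random effects, and the Cox specification has no planned site term.

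**Working it through.** **Inputs from the protocol article.** Two sites; 80 randomized 1:1; 15% attrition, leaving 68 (34 per arm); PG-SGA SD 6–7; correlation of magnitude 0.55; three visits in the model; 4-point threshold for a clinically meaningful difference.

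**Assumed, because the document does not give them.** An equal site split; a within-patient correlation of 0.55 with compound symmetry; a range of true site differences.

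**1. The plan's own precision, as a yardstick.** Half-width = 1.96 × SD × √(2/34) × √(1 − 0.55²). SD 6 gives 2.38 and SD 7 gives 2.78, which reproduces the stated ±2.4–2.8. Only the square of the correlation enters.

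**2. How often the site variance is estimated at zero.** The variance is zero when F(1, 66) < 1. For a true site difference d, F is non-central with parameter d²/v0, where v0 = s²(1/34 + 1/34). Take SD 6.5.

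- Single visit: s² = 42.25, v0 = 2.485. For d = 2 the parameter is 4/2.485 = 1.61 and P(zero) = 0.38.
- Mean of three visits: s² = 42.25 × (1 + 2 × 0.55)/3 = 29.575, v0 = 1.740. For d = 2 the parameter is 4/1.740 = 2.30 and P(zero) = 0.30.
- d = 0, either case: P(zero) = 0.68.

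The alternative is to treat site effects as random with between-site SD τ. Then P(zero) is the central F(1, 66) distribution function at v0/(v0 + 2τ²). Using the three-visit mean and SD 6–7:

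| τ (points) | P(zero) |
|---|---|
| 0 | 0.68 |
| 1 | 0.48–0.52 |
| 2 | 0.31–0.35 |
| 3 | 0.22–0.25 |

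Using N = 80 or a 70:30 site split moves these by about 0.02. A REML simulation of the full three-visit model (68 patients, SD 6.5, 150 runs per setting) gave 0.66, 0.55 and 0.31 at τ = 0, 1 and 2.

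**3. How precise the site SD is.** With 1 df, the chi-square 95% limits for the SD of the site means are 0.45 and 31.9 times the estimate. In the simulation at τ = 2, the 5th to 95th percentile of the estimated site SD was 0 to 4.9.

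**4. Effect on the treatment estimate, site random versus site fixed.**

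- Complete data: the group-by-time estimates agree to within 1e-13. Mean SEs are 1.49 v 1.49, 1.50 v 1.50 and 1.48 v 1.48 at τ = 0, 1 and 2.
- 15% attrition (simulated): the interaction estimates differ by at most about 0.06 points. The arm difference at a single visit differs by up to about 0.3 points.

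**5. Chance imbalance on site.** Assume 40 patients per site and 40 per arm overall. The hypergeometric probability of a 24:16 or worse split at a site is 11.7%. Simulating four strata with blocks of 4 and 6 gives about 12–13%.

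At exactly 24:16 in one site and 16:24 in the other, the arms differ by 24/40 − 16/40 = 0.2 in site share. An assumed 3-point site difference would then shift an unadjusted single-time-point comparison by 3 × 0.2 = 0.6 points.

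**The case against.** The case for leaving the text alone is substantial.

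- **The plan's main contrast is safe.** Site is constant within a patient, so a site intercept cancels from the group-by-time contrast with complete data. A reader might infer that every mixed-model estimate is distorted; step 4 shows otherwise. This part of the objection stands.
- **There is some protection against imbalance.** A reader might infer that, without site stratification, nothing guards the arm comparison. The covariate clause would bring site in if the arms differed on it, and the Cox model has a similar clause. This stands in part: the protection exists, but it is triggered by observed imbalance and is not fixed in advance.
- **Much of the collapse is harmless.** The most frequent case, 68%, is the one with no site difference to adjust for. The other scenarios are assumptions. This stands, although 30–40% at a 2-point difference is still a high rate for losing a term the plan meant to keep.
- **The imbalance is modest.** Simple randomization would give about 27% for 24:16 or worse, but this trial uses stratified blocks and the relevant figure is about 12%. The 0.6-point shift in step 5 is small beside the ±2.4–2.8 precision and the 4-point threshold.
- **Convergence.** A reader might expect convergence failures. None was shown, and a fit with zero site variance still gives usable fixed-effect estimates.

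Handling of a singular fit could be left to an analysis plan that is not shown. The choice of a random effect for two named sites, however, is stated here, so it is open to comment as a choice.

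**Conclusion.** The point holds as a minor one. Two sites cannot support a useful variance estimate. It will often be zero: about 70% of trials with no site difference and 30–40% with an assumed 2-point difference. The random effect also gives no workable site adjustment in a standard GEE, and none is planned for the Cox model.

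The consequence is limited to the site adjustment of single-time-point, binary and time-to-event arm comparisons under chance imbalance, and to any use of the site variance in planning the next trial. The PG-SGA group-by-time result is essentially untouched, and so are the descriptive feasibility and acceptability outcomes that are primary.

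The figures rest on assumed site differences, roughly equal site sizes and a within-patient correlation of 0.55. The document gives no between-site difference against which to check them.

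**What to change.** In the Aim 2 analyses, replace the random site effect with a fixed two-level site indicator. Specify it in advance for the mixed, GEE and Cox models, whether or not the arms turn out balanced on site. Keep the patient-level random effect or residual covariance for the repeated measures.

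The cost is one degree of freedom and a one-line change of wording. The complete-data simulation showed no loss of precision for the group-by-time estimate. The randomization scheme need not change. The edit is best made before outcome data are examined by arm.

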#### Sample size considerations

The goal of this pilot randomized controlled trial is to assess feasibility of study procedures and feasibility of the implementation strategy prior to a definitive hybrid implementation-effectiveness trial. We will recruit 80 patients, assuming 15% will be lost due to attrition based on our prior studies, leaving a sample size of 68 (34 patients per arm). Guidance for conducting pilot randomized trials suggests 25–35 participants per arm is sufficient to estimate feasibility outcomes, such as recruitment and retention, and to provide preliminary estimates of intervention effect and variation [130–132]. Consistent with NIH guidance, this pilot trial is not powered for definitive hypothesis testing; the sample size selection is based on the goal of estimating feasibility outcomes and providing preliminary intervention effect estimates [133]. Nonetheless, with 68 patients, the study is powered to estimate mean change in PG-SGA score with reasonable precision (CI ± 2.4–2.8 points) depending on the standard deviation assumption (6–7 based on prior studies) [107] and an assumption of *r*=-.55 based on prior studies [134]. 

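### The stated ±2.4–2.8 point precision for PG-SGA change matches a baseline-adjusted analysis; the planned group × time model gives about ±2.7–3.2, or ±2.9–3.3, depending on what r means

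*Protocol article*

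**What the plan says.** All references are to the protocol article.

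- **Sample size considerations.** "We will recruit 80 patients, assuming 15% will be lost due to attrition based on our prior studies", which leaves 68, or 34 per arm. With these patients "the study is powered to estimate mean change in PG-SGA score with reasonable precision"; the half-width is given as ±2.4–2.8 points, for an SD of 6 to 7 and "an assumption of *r*=-.55 based on prior studies". The text does not say whether the SD is that of the score or of the change, or which two measurements r links.
- **Randomization.** Patients "will be 1:1 randomized to the STRONG program versus usual care".
- **Aim 2 analyses.** PG-SGA is analysed at baseline, 3 and 6 months with a linear mixed model. "The model will include fixed effects for time, group, and group X time", and "A group X time interaction will provide evidence for differential change by treatment groups". Randomization strata and unbalanced characteristics are covariates, and site is a random effect. Baseline PG-SGA is not named as a covariate, and the arms are not constrained to share a baseline mean. Mean differences are to be compared with a 4-point threshold.
- **Secondary effectiveness outcomes.** PG-SGA is the intended primary effectiveness outcome of the later definitive trial.

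**The concern.** A precision statement should describe the analysis that will be run. The printed half-width is what one obtains by conditioning on baseline, which multiplies the SD by √(1−r²). The Aim 2 model does not condition on baseline. Baseline is one of its outcomes, with its own group effect, so group × time at a given visit compares raw changes between arms. That contrast is less precise whether r is a baseline–follow-up or a baseline–change correlation.

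The stake is limited but real. This is the section's only numerical precision claim, and it concerns the outcome meant to be primary in the next trial. As written, readers will expect a somewhat tighter interval than the planned single-visit contrast gives. An unexplained r could also be carried into later planning with the wrong meaning.

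**Working it through.** **Inputs.** From Sample size considerations: 80 × 0.85 = 68, or 34 per arm (the attrition arithmetic is correct); SD 6 and 7; |r| = .55. Assumptions: a two-sided 95% interval with z = 1.96, and, for the score-based calculations, the same SD at baseline and follow-up.

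**Common form.** Half-width = 1.96 × SD × √(2/34) × f, where f depends on the analysis. Since √(2/34) = 0.2425, the part before f is 2.852 for SD 6 and 3.328 for SD 7.

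**Step 1: reproduce the printed figure.** Adjusting for baseline gives f = √(1 − .55²) = √0.6975 = 0.835.
- SD 6: 2.852 × 0.835 = 2.38
- SD 7: 3.328 × 0.835 = 2.78

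This is the stated 2.4–2.8. A t quantile gives 2.43–2.83, which rounds to the same figures. Because r is squared, its sign has no effect here.

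**Step 2: the planned contrast, r = +.55 between baseline and follow-up.** The variance of a raw change is 2·SD²·(1 − r), so f = √(2 × 0.45) = √0.9 = 0.949.
- SD 6: 2.852 × 0.949 = 2.71
- SD 7: 3.328 × 0.949 = 3.16

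The ratio to Step 1 is √(0.9/0.6975) = 1.136, so the interval is 14% wider, or 0.3–0.4 points.

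**Step 3: the planned contrast, r = −.55 between baseline and change, SD 6–7 being that of change.** An unadjusted comparison of changes has f = 1, giving 2.85 and 3.33. The ratio to Step 1 is 1/0.835 = 1.197, so the interval is 20% wider, or about 0.5 points. Baseline adjustment on this reading still gives 2.38–2.78.

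**Step 4: check on the full three-visit model.** Generalised least squares with three categorical visits, an exchangeable correlation of +.55 and 34 complete patients per arm gives, at 3 or at 6 months:

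| Fixed effects | SD 6 | SD 7 |
|---|---|---|
| Time, group, group × time (as planned) | 2.71 | 3.16 |
| Same, baseline means constrained equal | 2.38 | 2.78 |

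The second follow-up visit therefore does not close the gap for a single-visit contrast, and constraining baseline closes it exactly.

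**Step 5: use of dropouts' baselines.** The mixed model keeps incomplete patients. With 40 baselines and 34 follow-ups per arm, the variance factor is 2 × [0.6975/34 + 0.45²/40] = 0.05115, and 1.96 × SD × √0.05115 = 2.66 and 3.10. The gap shrinks only slightly.

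**The case against.** **The origin of the figure is inferred.** No formula is printed, and baseline adjustment is not the only calculation that rounds to 2.4–2.8. A 90% interval that ignores r gives 2.39–2.79, but the text says the figure rests on r. A 95% t-based contrast of the average of the 3- and 6-month changes at an exchangeable r = +.55 has variance factor (1.55/2) + 1 − 1.10 = 0.675 and also gives 2.39–2.79. The planned model could supply that average, but the article does not describe it. This objection stands: the mismatch is shown for a single-visit contrast, and baseline adjustment is the likely source rather than a proven one.

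**The minus sign may be correct.** A reader might infer that a negative r roughly doubles the interval. Taking −.55 as the baseline–follow-up correlation gives f = √3.1 = 1.761 and half-widths of 5.02–5.86, above 4 points. The document does not support that reading. It never says what r links, and a negative baseline–change correlation is ordinary regression to the mean. A common −.55 across three visits is not even a valid correlation matrix (smallest eigenvalue 1 − 2 × .55 = −0.10). The sign may also be a misprint or a text-conversion artefact. A sign error is therefore unproven.

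**Covariates might supply the adjustment.** Strata and unbalanced characteristics enter as covariates. With complete data, however, main effects of characteristics that are fixed within a patient do not alter a within-patient group × time contrast, so this does not recover the stated width.

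**Little depends on it.** The sample size is justified by feasibility and by guidance on numbers per arm, the article disclaims definitive testing, and none of the Table 3 benchmarks uses PG-SGA. The planned model is also a valid analysis of change, only less efficient. All of this stands and limits the weight of the point.

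**Conclusion.** The stated precision and the planned model do not match for a single-visit contrast. On the printed inputs the half-width is about ±2.7–3.2 if r is +.55 between baseline and follow-up, or about ±2.9–3.3 if −.55 is a baseline–change correlation with SD 6–7 for the change. The printed ±2.4–2.8 applies once baseline is adjusted for or constrained. This rests on a 95% level, 34 completers per arm and, for the first range, equal SDs over time.

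The issue is moderate. Every realistic value stays below 4 points, so the claim of reasonable precision survives with a somewhat larger number. A reader might also infer that the trial is too small; it is not sized on this figure, so no case for more patients follows. Nor does the document support a conclusion that the interval exceeds the clinical threshold.

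**What to change.** 1. **Preferred: align the model with the figure.** In Aim 2, either constrain baseline PG-SGA means to be equal across arms and keep a group effect at each post-baseline visit, or use baseline PG-SGA as a covariate with only the 3- and 6-month values as outcomes. Then ±2.4–2.8 applies.
2. **If the current model is kept,** restate the figure as about ±2.7–3.2 (r = +.55 between baseline and follow-up), or about ±2.9–3.3 if r is the baseline–change correlation and the SD is that of change.
3. **In either case,** state the confidence level, the contrast and visit, whether the SD is of the score or of the change, and which measurements r links. Change the sign to +.55 only if the source confirms that r is the baseline–follow-up correlation.

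The cost is wording in two paragraphs and, for the first option, one changed model line. Baseline PG-SGA is already collected, so no further patients or data are needed, and the first option also yields a tighter estimate.

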#### Data monitoring, analysis, and security

The PI and study staff will meet weekly to review study feasibility and acceptability (e.g., recruitment) and adherence to study procedures and potential protocol deviations. The study team will review other key quality metrics with the entire study team (e.g., participant satisfaction) on a quarterly basis. If any problems are observed (e.g., feasibility benchmark not obtained), the study team will review procedures and consider modifying the protocol if necessary. The proposed study is minimal risk and will not require external safety monitoring. Nonetheless, the study team will use the following procedures to monitor risk: (1) prompting patients to report any problems related to the study protocol (e.g., burden); (2) maintaining an adverse event log; and (3) following institutional and funder policies for prompt reporting of serious or unanticipated adverse events and pausing the study protocol if necessary. The study team will follow institutional data security procedures (e.g., minimizing use of protected health information) to protect participant data.

#### Design considerations

We chose to include all patients with a diagnosis of gastric or esophageal cancer given the high prevalence of malnutrition and nutrition-impact symptoms (e.g., swallowing difficulty) in this patient population, as opposed to screening for malnutrition and only including individuals who screen positive for malnutrition (e.g., a disease-based approach versus a triggered approach) [1–6]. Historically, a screen and referral approach has been recommended for all oncology patients but may not be fitting for patient populations where malnutrition is nearly universal (not something that varies across patients).

### Dissemination and future research

Study findings will be disseminated through required updates for ClinicalTrials.gov and a plain language summary of study findings that will be shared with patient participants, clinic team members, and other key stakeholders. Study findings will also be shared through conference abstracts and peer reviewed publications. Findings from the study will support a definitive hybrid-implementation trial. At the conclusion of the study, de-identified data will be deposited in the UNC Dataverse repository to facilitate data sharing.

### Patient, caregiver, and clinician involvement

The STRONG intervention was developed based on extensive data gathering and iterative testing with patients, caregivers, and clinicians through qualitative research and user-centered design, findings that will be reported elsewhere.

## Discussion

Pilot studies play a critical role in implementation research by ensuring that strategies and proposed study methods are feasible prior to conducting a larger and more costly definitive trial [135]. This pilot study will assess the feasibility of a patient-mediated implementation strategy to improve nutrition care delivery for esophageal and gastric cancer patients, who have a high burden of malnutrition [1–6]. The study is timed to deliver support to patients during neoadjuvant therapy prior to surgery, when nutrition care plays a pivotal role in long-term outcomes [44–47]. In the future, we aim to expand the program to individuals diagnosed with metastatic gastric and esophageal cancer who are receiving palliative chemotherapy, who may also greatly benefit from nutrition counseling. There has been limited research on implementation strategies designed to overcome barriers to delivering nutrition care during cancer treatment [136]. Additionally, there has been limited research on patient-mediated implementation strategies as an approach to increase evidence-based care delivery [66]. Positive findings from this line of research could expand the reach of evidence-based nutrition care during cancer treatment and improve patients’ nutritional status, quality of life, treatment tolerance, and survival.

**Table 2 Tab2:** Nutrition counseling content

Section	Content
Nutrition assessment	Detailed review of weight history, food intake, physical function, nutrition-impact symptoms, micronutrient deficiencies, medical history related to nutrition, treatment plan, relevant labs
Social needs	Screening for food insecurity and other barriers to nutrition
Food preferences	Discussion about foods individual typically eats, cultural, religious, or other dietary preferences
Physical activity	Review of physical activity
Goal setting and values clarification	Determine patient goals for improving nutrition and/or function and motivation for behavior change (e.g., quality of life)
Energy and protein requirements	Estimate requirements for calorie and protein intake
Nutrition counseling and education	Provide patient with dietary strategies based on nutrition problems (e.g., meal planning with nausea), recommended interventions (e.g., supplements, referrals), and education as needed (e.g., high quality protein sources)
Follow up	Review next steps, remind patient of what should be done between visits (e.g., food and symptom diary) and timing of next appointment

**Table 3 Tab3:** Pre-planned benchmarks for pilot trial

Measure	Benchmark
**Recruitment**: Proportion of eligible patients who consent to participate	≥ 50%
**Data Completion**: Proportion of patients who complete all study assessments	≥ 70%
**Retention**: Proportion of patients who are retained at the end of the intervention	≥ 85%
**Counseling adherence**: Proportion of patients who attend the majority (3/4) dietitian visits	≥ 70%
**Logging adherence**: Proportion of patients who log food intake and symptoms ≥ 3 days a week for study period	≥ 70%
**Question prompt list usage**: Proportion of patients who report using question prompt list	≥ 70%
**Educational brochure usage**: Proportion of patients who report using educational brochure	≥ 70%
**Fidelity**: Dietitian adherence to prescribed elements of counseling outlined in checklist	≥ 80%
**Acceptability**: Proportion of patients who report high satisfaction with intervention	≥ 80%
**Perceived usefulness**: Proportion of patients who report question prompt list was useful for patient-dietitian discussions	≥ 80%

